### Participating hospitals

One University hospital in Belgium and five Dutch general hospitals will participate in this trial and enroll patients.

### Randomization

After patients have consented for participating in this study, randomization will be performed by the coordinating researcher centrally through a website using a computer-generated randomization table. The subjects are assigned in a 1:1 ratio to either vaginal sacrospinous hysteropexy or laparoscopic sacrohysteropexy. The randomization will be stratified according to the center and severity of prolapse (POP-Q stage 2, 3 or 4). The order of outcomes is unknown to the investigators or to the participating gynecologists. Data will be kept anonymous. The subjects will be informed about the allocated operative procedure shortly after the randomization. Subjects that withdraw after randomization will be treated according to the preference of the gynecologist.

### Data collection

All patients will undergo routine gynecological examination, which is part of the standard procedure before surgery. This examination includes pelvic ultrasound to exclude uterine or ovarian disease, routine PAP-smear and vaginal inspection in 45° semi-upright position for staging uterovaginal prolapse by a POP-Q examination. Maximum prolapse is demonstrated and identified by asking the patient to cough and to perform a Valsalva maneuver while each vaginal wall is individually exposed.

To obtain baseline characteristics of both patients groups all patients are asked to fill in standardized questionnaires at inclusion. These questionnaires are validated quality of life questionnaires (RAND 36, Euroqol 5D, Urogenital Distress Inventory, Defecatory Distress Inventory, Incontinence Impact questionnaire) and two questionnaires regarding sexual functioning (Pelvic Organ Prolapse/Urinary Incontinence Sexual Questionnaire and selected items from the “Vragenlijst Seksuele Disfuncties”) [21–29]. Preoperative urodynamic evaluation is only performed in women with bladder dysfunction.

During hospitalization and in the first 6 weeks after surgery patients are asked to keep a diary which contains the following items: postoperative pain measured by Visual Analogue Score (VAS), used pain medication and the RI-10 recovery questionnaire. The RI-10 recovery questionnaire is a validated quality of life questionnaire measuring subjective postoperative recovery [30]. To prevent a recall bias as much as possible, patients will be phoned two and four weeks after surgery as a reminder to fill in the diary. After surgery, patients will visit the hospital at 6 weeks (routine post-operative consultation), 6 months, 12 months and yearly thereafter. The total duration of the follow-up is 5 years. Each check-up includes a standardized written questionnaire regarding quality of life and sexual functioning (similar to the questionnaires at baseline) and a clinical examination (including POP-Q).

The validated questionnaires will be administered by the participating hospitals (baseline and 6 weeks postoperative) and by the coordinating hospital (6 months postoperative and yearly thereafter).

### Interventions

Eligible women will be randomly allocated to receive either a laparoscopic sacrohysteropexy or a vaginal sacrospinous hysteropexy. The vaginal procedure can be performed under general or spinal anesthesia, according to the preference of patient and anesthesiologist. The laparoscopic procedure will be performed under general anesthesia. All women receive peri-operative antibiotics and thrombosis prophylaxis. Post-operatively a bladder catheter is placed and removed after one day. Patients will receive analgesics if necessary in accordance with local hospital protocol. All patients are advised to abstain from heavy physical work for a minimal period of 6 weeks.

In order to standardize both procedures and prevent variation in procedures, a protocol has been developed for both surgical procedures. All procedures are performed according to this standardized protocol and also all participating hospitals use the same materials for the procedures (e.g. sutures, mesh). At least twenty procedures must have been performed by participating gynecologists to eliminate a learning curve effect. It is allowed for participating gynecologists to partner with a colleague gynecologist: one gynecologist can perform the laparoscopic sacrohysteropexy and the other gynecologist can perform the vaginal sacrospinous hysteropexy.

#### Laparoscopic sacrohysteropexy

The patient is placed in lithotomy position. An uterine manipulator (Clearview, Clinical Innovations LLC, Murray, UT, USA) is placed to provide visualization of the surgical site.

Four laparoscopic ports (umbilical, suprapubic, two lateral ports) will be placed and a pneumoperitoneum will be created. The colon sigmoid can be removed from the operating field by attaching it to the abdominal wall by a suture through some plica epiploica. The peritoneum over the sacral promontory will be incised; the right ureter will be identified. Each broad ligament at the level of the cervico-uterine junction will be opened. The vesico-uterine peritoneum will be incised and the bladder will be dissected distally for 2–3 cm. A bifurcated polypropylene flat mesh (Gynemesh, Ethicon Inc, Sommerville, NJ, USA) will be used. The arms of the mesh will be introduced bilaterally through windows created in the broad ligaments. Permanent sutures (Mersilene 2.0, Ethicon, Sommerville, NJ, USA) will be placed through the arms of the mesh and the anterior cervix (2–3 sutures) and the posterior cervix (4 sutures). The surgeon is allowed to place the mesh further down the anterior and posterior vaginal wall to treat compartment specific prolapses. The mesh will be tacked to the sacral promontory using 5.3 × 3.7 mm titanium staples (Endoscopic Multifeed Stapler-20, Ethicon Inc, Sommerville, NJ, USA) to elevate the uterus (3 staples). The peritoneum will be closed with 5.3 × 3.7 mm titanium staples (Endoscopic Multifeed Stapler-20, Ethicon, Sommerville, NJ, USA) covering the promontory part of the mesh and a running suture (Vicryl 2.0, Ethicon Inc, Sommerville, NJ, USA) covering the cervical part of the mesh. The laparoscopic ports will be removed and the wounds will be closed. Vaginal examination after the laparoscopic hysteropexy is part of the protocol and additional anterior and/or posterior colporrhaphy or incontinence surgery can be performed if necessary, according to the standard procedures of the hospital.

#### Vaginal sacrospinous hysteropexy

The patient is placed in lithotomy position. Access to the sacrospinous ligament is obtained through the pararectal space. The posterior vaginal wall will be incised and separated from the rectum. The right ischial spine will be localized digitally and after retractor positioning, the ligament is made visible through blunt dissection. Two permanent sutures (Prolene 1.0, Ethicon Inc, Sommerville, NJ, USA) will be placed under direct vision through the right sacrospinous ligament at least 2 cm from the ischial spine. Hereafter, an additional anterior and/or posterior colporrhaphy or incontinence surgery can be performed, according to the standard procedures of the hospital. The permanent sutures will be placed through the posterior side of the cervix and two thirds of the posterior vaginal wall will be closed with absorbable sutures (Vicryl 2.0, Ethicon Inc, Sommerville, NJ, USA). The permanent sutures will be tightened and the cervix will be redressed. The remainder of the vaginal wall will be closed.

### Statistical analysis

#### Sample size and power calculations

Sample size calculation was performed using Sample Power 2.0 (SPSS inc. Chicago, IL, USA). The aim of the study is to clarify whether laparoscopic sacrohysteropexy and vaginal sacrospinous hysteropexy do not differ significantly in surgical success rates of the apical compartment. We aim to demonstrate non-inferiority of the laparoscopic sacrohysteropexy at both 1 and 5 year (i.e. two tests on the primary endpoint will be performed). Two groups of 55 patients will be included to yield a 80% power for a non-inferiority margin of 10% assuming a recurrence rate of prolapse at the apical compartment of 3%. Taking into account 10% attrition, a number of 62 patients will be included in each study arm. This dropout can be expected when patients, after randomization, are unhappy with their allocated treatment and choose to end their participation in the study or due to incomplete or lost data. A total number of 124 women will be included in this study.

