**Methods:**

The LAVA trial is a randomized controlled multicenter non-inferiority trial. The study compares laparoscopic sacrohysteropexy with vaginal sacrospinous hysteropexy in women with uterine prolapse stage 2 or higher. The primary outcome of this study is surgical success of the apical compartment at 1 and 5 years follow-up. Secondary outcomes are subjective improvement on urogenital symptoms and quality of life (assessed by disease-specific and general quality of life questionnaires), complications following surgery, hospital stay, post-operative recovery, sexual functioning and costs-effectiveness. Evaluation will take place pre-operatively, and 6 weeks, 6 months, 12 months and annually till 60 months after surgery. Validated questionnaires will be used.

Analysis will be performed according to the intention to treat principle. Based on comparable recurrence rates of 3% and a non-inferiority margin of 10%, 62 patients are needed in each arm to prove the hypothesis with a 95% confidence interval.

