#### Data analysis

The analysis will be performed by intention to treat, and stratified for center and severity of prolapse. Patient characteristics will be summarized using descriptive statistics for continuous variables (mean ± standard deviation, minimum, maximum and sample size) and frequency tables for categorical variables (numbers and percentages).Statistical analysis of the data will be conducted at 12 and 60 months follow-up.

Surgical success of the apical compartment at 1 and 5 years follow-up in both study groups will be considered as the primary outcome. Success is defined as position of the cervix at or above the mid-vagina (C < -TVL/2), no symptoms (defined as no symptoms of vaginal bulging and protrusion on the validated questionnaire) and no reoperation or pessary use for recurrent apical prolapse. Failure in one of these areas will constitute a failure. Non-inferiority of laparoscopic sacrohysteropexy to vaginal sacrospinous hysteropexy will be concluded if the 95% confidence interval (CI) does not exceed the non-inferiority margin of 10% (Figure 2, scenario B). If the whole 95% CI exceeds the non-inferiority margin of 10%, the laparoscopic sacrohysteropexy will be considered to be inferior (scenario C). If the 95% CI for the difference in surgical success rates lies left from zero, it can be concluded that there is evidence of superiority of laparoscopic sacrohysteropexy over vaginal sacrospinous hysteropexy (scenario A) [31, 32].

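### The 55 per arm does not follow from the 95% confidence interval used to judge non-inferiority, and the 80% power is not tied to the stated aim of success at both 1 and 5 years

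*Protocol article*

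**What the plan says.** The section on sample size and power sets the goal: "We aim to demonstrate non-inferiority of the laparoscopic sacrohysteropexy at both 1 and 5 year", and adds in brackets "i.e. two tests on the primary endpoint will be performed". It then gives the size: "Two groups of 55 patients will be included to yield a 80% power for a non-inferiority margin of 10" percent, "assuming a recurrence rate of prolapse at the apical compartment of 3" percent. An allowance of 10% for attrition raises 55 to 62 per arm, 124 in total. No significance level appears in that section.

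The confidence level is given in two other places. The Abstract (Methods) ties the sample size to it: "62 patients are needed in each arm to prove the hypothesis with a 95% confidence interval". The Data analysis section states that non-inferiority "will be concluded if the 95% confidence interval (CI) does not exceed the non-inferiority margin of 10" percent. It places the analyses at 12 and 60 months. It gives no adjusted level, and it does not say how the two results combine into one conclusion.

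**The concern.** A non-inferiority sample size is fixed by the event rate, the margin, the power and the one-sided error rate. The article gives the first three, and the 95% interval implies the fourth (one-sided 0.025). Together they do not lead to 55, so the calculation and the decision rule appear to use different error rates.

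This matters for two reasons. First, the confidence level helps decide whether the primary claim is met: the same data can pass at 95% and fail at 97.5%. Second, it is unclear what the 80% refers to. If both time points must succeed, no alpha split is needed, but the relevant figure is the joint power. If each time point supports a claim of its own, the error rate over two tests needs control, and the written rule has none. The combination rule should be settled before the 12-month results are seen.

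**Working it through.** **Inputs.** Failure rate 3% in both arms (Abstract: "Based on comparable recurrence rates of 3% and a non-inferiority margin of 10" percent; same rate in the sample-size section); true difference 0; margin 0.10; power 80% (z = 0.8416); 1:1 allocation; attrition 10%. Alpha for the calculation is not stated; the decision rule implies one-sided 0.025.

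**Formula (unpooled variance).** n per arm = (z_α + 0.8416)² × 2 × 0.03 × 0.97 / 0.10² = (z_α + 0.8416)² × 5.82.

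| One-sided alpha | Matching two-sided interval | n, plain | n, continuity-corrected |
|---|---|---|---|
| 0.05 | 90% | 36.0 | 54.1 (55 rounded up) |
| 0.025 | 95% | 45.7 (46 rounded up) | 64.1 (65 rounded up) |
| 0.0125 | 97.5% | 55.3 (56 rounded up) | 74.0 |

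**Reproducing 55.**
- One-sided 0.0125, plain: 55.3. Power at 55 is 79.7%.
- One-sided 0.05, continuity-corrected: 54.1, rounded up to 55. Exact power of a score test at this level with 55 per arm is 79.9%.
- One-sided 0.025: no variant tried gives 55. Plain gives 46, continuity-corrected 65, and a restricted-variance score calculation 78. The plain formula reaches 55 only if the failure rate is about 3.6% instead of 3%.

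**Attrition.** 55/0.9 = 61.1, so 62; this step is correct. For the 95% interval, 46/0.9 = 51.1, so 52.

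**Power per time point with 55 per arm and a 95% interval.** SE = √(2 × 0.03 × 0.97/55) = 0.0325; 0.10/0.0325 = 3.074; 3.074 − 1.960 = 1.114; power = 86.7%. Exact binomial enumeration with Wald limits gives 84.9%.

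**Joint power for both time points with 55 per arm.** Assumptions: 3% failure in each arm at each time point and Wald limits. A given share of 1-year failures is still failing at 5 years, with new failures keeping the 5-year rate at 3%. Simulation with 400,000 replicates:

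| Persistence of 1-year failures | 95% intervals | 97.5% intervals |
|---|---|---|
| None beyond chance (independent) | 72% | 65% |
| 50% | 76% | 70% |
| 90% | 82% | 77% |
| All | 85% | 81% |

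The article gives no figure for persistence. A normal approximation with 95% intervals runs from 75.2% (correlation 0) to 86.7% (correlation 1), passing 80% at a correlation of about 0.7.

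**Family-wise error if either time point suffices.** With unadjusted 95% intervals and independent tests, 1 − 0.975² = 4.9% one-sided; the bound without independence is 2 × 2.5% = 5%. Overlap between the two results in the same women would lower it.

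**The case against.** The strongest counter-argument is that nothing is under-sized: measured against a single 95% interval with Wald limits, 55 exceeds the 46 needed. That stands for one comparison. It does not make the stated 80% correct, and it does not settle the two-test aim.

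A reader might infer that the authors applied a Bonferroni split and then forgot it in the decision rule. The remark that "two tests on the primary endpoint will be performed" fits that, but the article never mentions a split, 0.0125 or a 97.5% interval. Strict rounding would give 56, and one-sided 0.05 with continuity correction reaches 55 as well. The cause is therefore unknown; only the mismatch with 95% is shown.

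A reader might also infer that power for the stated aim is below 80%. The article does not establish this: under the written 95% rule the range crosses 80%. The success definition counts reoperation and pessary use for recurrence, so substantial persistence is plausible. Full persistence with 3% at both times would, however, mean no new failures in four years.

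Nor is inflated type I error established. If both time points must succeed, as the stated aim suggests, unadjusted 95% intervals cause none. Analysing at 12 and 60 months fixes the timing; it does not by itself create two separate claims.

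Finally, one could lower the joint power further by taking a higher 5-year failure rate, for instance from the 93.1% cure rate cited in the Background. That figure comes from an observational study for which the article gives no five-year time point. It raises a separate question about the assumed rate and is not used here.

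**Conclusion.** The point holds as an inconsistency between stated figures. Under the usual unpooled calculation, the 95% interval calls for 46 per arm (52 after attrition), and 55 gives about 85–87% power per time point instead of 80%. The alpha behind 55 is not stated, and neither of the alphas that reproduce it (0.0125 or 0.05, one-sided) corresponds to a 95% interval.

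The 80% matches a single-test calculation only. For the stated aim at both time points, power with 95% intervals is about 72% to 85% depending on persistence, so 80% is possible but not assured.

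These sizes rest on 3% failure in both arms at both times and on Wald limits. A score-type interval would be more demanding: exact power at 55 and one-sided 0.025 would be 65% per test. The mismatch itself does not depend on that choice, since no variant tried at one-sided 0.025 yields 55.

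A later analysis plan could choose the interval method and the combination rule. It could not make the published 55, 80% and 95% agree without changing one of them.

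**What to change.** In line with the aim in the sample-size section:

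1. In Data analysis, state that overall non-inferiority is claimed only if the 95% intervals at both 1 and 5 years exclude the 10% margin. No alpha split is then needed.
2. In the sample-size section, state one-sided alpha 0.025. Replace 80% by the per-test power (about 85–87% with 55 per arm) and the joint-power range (about 72% to 85%), naming the persistence assumption and the interval method.

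If instead each time point is meant to support its own claim, use a 97.5% interval at each in the Abstract and in Data analysis, and state one-sided alpha 0.0125 with about 80% power per test. This option fits the stated aim less well: success at both would then have a probability of about 65% to 81% over the same persistence range.

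Either route takes a few sentences and no extra patients. The cost is a restated power in the first case and a slightly wider interval in the second. The choice should be recorded before the 12-month analysis.

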One procedure for uterine descent with uterine preservation is vaginal sacrospinous hysteropexy. In this procedure, the uterus is suspended to the sacrospinous ligaments with permanent sutures. In several studies, this technique was demonstrated to be a safe procedure for the primary treatment of uterine descent [9–11]. In a prospective observational study of 72 women with uterine descent, sacrospinous hysteropexy significantly reduced all urogenital and several defecatory symptoms and significantly improved quality of life. It also cured the uterine descent in 93.1% of women [12]. The procedure is associated with a few serious complications. The most common complication is buttock pain on the side where the sacrospinous sutures have been passed, this occurs in approximately 10-15% of the women, but resolves typically in days to months. One prospective study and one retrospective study comparing vaginal hysterectomy to vaginal sacrospinous hysteropexy demonstrated no significant difference in anatomical outcome, while hospital stay was shorter, less pain was experienced and recovery was quicker in the latter group [13–15]. These studies conclude that vaginal sacrospinous hysteropexy is associated with a faster complete recovery compared to vaginal hysterectomy. In both groups high recurrence rates of anterior vaginal wall prolapse were demonstrated (50% in hysterectomy group vs. 65% in sacrospinous hysteropexy group) [15]. It is believed that the change in axis of the vagina after a sacrospinous hysteropexy predisposes to an increased risk of prolapse of the anterior compartment [16].

Another procedure for uterine descent with uterine preservation is laparoscopic sacrohysteropexy. In this procedure, the uterus is elevated by attaching the cervix to the sacral promontory using a mesh. One prospective study suggests that sacrohysteropexy is a safe and effective procedure. One out of 13 women (7.7%) had a recurrence of uterine prolapse (mean follow-up 15.6 months) [17]. However, in this study the sacrohysteropexy was performed by laparotomy.

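### The 80% power is computed for 3% apical recurrence, but the primary endpoint is a broader composite failure tested at 1 and 5 years, and power falls below 80% once that failure rate passes about 3% to 3.6%

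*Protocol article*

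**What the plan says.** Under Sample size and power calculations, the protocol article states: "Two groups of 55 patients will be included to yield a 80% power for a non-inferiority margin of 10" percent, "assuming a recurrence rate of prolapse at the apical compartment of 3" percent. It then allows for losses: "Taking into account 10% attrition, a number of 62 patients will be included in each study arm". The Abstract (Methods) turns this into a statement of need: "Based on comparable recurrence rates of 3% and a non-inferiority margin of 10%, 62 patients are needed in each arm". No source or time point is given for the 3%. The same section announces two tests of the primary endpoint, at 1 and 5 years, and the single rate serves both.

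Primary and secondary outcomes, and again Data analysis, define success by three conditions: cervix at or above mid-vagina, no bulging or protrusion symptoms on the questionnaire, and no reoperation or pessary for recurrent apical prolapse. Failing any one makes the woman a failure. Non-inferiority is concluded if the "95% confidence interval (CI) does not exceed the non-inferiority margin of 10" percent.

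The Background cites three apical results:
- Vaginal sacrospinous hysteropexy, the control procedure, in 72 women: "It also cured the uterine descent in 93.1% of women".
- Sacrohysteropexy by laparotomy: "One out of 13 women (7.7%) had a recurrence of uterine prolapse (mean follow-up 15.6 months").
- Laparoscopic sacrohysteropexy in 51 women: no objective recurrence, at 10 weeks.

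**The concern.** The planning rate and the endpoint describe different events. The 3% is a rate of apical recurrence. The endpoint counts that kind of event through cervix position and adds two further routes to failure. A composite in which any component suffices is at least as frequent as each of its components. The symptom component, as worded, is not restricted to an apical cause, and the Background reports 65% anterior-wall recurrence after sacrospinous hysteropexy, which may itself cause bulge symptoms. Reoperations also accumulate between year 1 and year 5, yet the same 3% is used at both.

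This matters because the variance of a risk difference rises almost in proportion to the failure rate when that rate is small, while the margin stays at 10 percentage points. A modest error in the planning rate therefore costs much power. The cost is an inconclusive trial (scenario D in Figure 2), not a false claim of non-inferiority. Readers of the article would meanwhile believe that 62 per arm are enough.

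**Working it through.** **Inputs.** Evaluable n = 55 per arm, margin 0.10, 80% power, 3% failure and 10% attrition (Sample size and power calculations); equal rates in both arms (Abstract, Hypothesis); allocation: "The subjects are assigned in a 1:1 ratio"; 95% interval (Data analysis). The sample-size section gives no alpha, so two values are carried:
- one-sided 0.025 (z = 1.960), matching the 95% interval;
- one-sided 0.0125 (z = 2.241), a 97.5% interval, as if alpha were split over the two announced tests. That split is an assumption.

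**Step 1: reproduce the plan.** With common failure rate p,

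n per arm = 2p(1−p) × (z + 0.842)² / 0.10²

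- p = 0.03, z = 2.241: 0.0582 × 9.505 / 0.01 = 55.3, against 55 stated.
- p = 0.03, z = 1.960: 0.0582 × 7.849 / 0.01 = 45.7, so 46.
- One-sided 0.05 with continuity correction gives 54.1, so the article does not settle which convention was used.
- Attrition: 55 / 0.90 = 61.1, so 62. This agrees.

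The stated size is therefore arithmetically sound at 3%.

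**Step 2: power of 55 per arm at other rates.**

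power = Φ(0.10 / √(2p(1−p)/55) − z)

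For p = 0.069: 2 × 0.069 × 0.931 / 55 = 0.002336, square root 0.0483, and 0.10 / 0.0483 = 2.069. Then Φ(2.069 − 1.960) = 0.54 and Φ(2.069 − 2.241) = 0.43.

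| Failure rate, both arms | Where it comes from | 95% interval | 97.5% interval |
|---|---|---|---|
| 3% | plan | 87% | 80% |
| 4.4% | three cited series pooled, (5+1+0)/(72+13+51) = 6/136 | 72% | 62% |
| 6.9% | control-procedure series, 100% − 93.1% (5/72) | 54% | 43% |
| 10% | assumed | 42% | 31% |

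**Step 3: the highest rate that keeps 80%.** Solve 2p(1−p) = 55 × 0.10² / (z + 0.842)².

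- z = 1.960: 0.55 / 7.849 = 0.0701, so p = 3.6%.
- z = 2.241: 0.55 / 9.505 = 0.0579, so p = 3.0%.

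With the convention that yields 55, there is no room above the planning rate.

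**Step 4: does the approximation drive this?** Exact enumeration of the binomial outcomes with 55 per arm and a Wald 95% interval gives 85% power at 3% and 59% at 6.9%. With a Newcombe 95% interval the figures are 65% and 44%. The fall is present under either method.

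**The case against.** The strongest defence is that nothing stated is false. The 80% is conditional on 3%, and at 3% it is right. The cited series are small, and their exact 95% intervals all include 3%: 2.3% to 15.5% for 5/72, 0.2% to 36.0% for 1/13, 0% to 7.0% for 0/51, and 1.6% to 9.4% for the pooled 6/136. The 7.7% is one woman in 13, operated by laparotomy. The 93.1% comes with no cure definition or follow-up time, and the trial's cervix criterion may be looser or stricter. The full protocol, not shown, may justify the 3%. If the laparoscopic arm did better, power would recover: 6.9% against 4.4% gives 81%, and 6.9% against 3% gives 92% (95% interval). If all 62 per arm were evaluable at 4.4%, power would be 77%.

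Most of this stands, and it limits the point. A reader might infer that the true failure rate is at least about 7%, that the real power is 54%, or that an inconclusive result is about as likely as not. The documents do not support any of these as fixed conclusions; each needs 6.9% or more in both arms, which one small series of unstated definition cannot establish.

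What the defence does not remove is the mismatch of events. The intervals above concern recurrence or cure of uterine descent, not the composite. The only cited rate below 3% is a 10-week result and says little about 1 or 5 years. The unequal-rate scenarios depart from the article's own premise of comparable rates. The absence of a source for the 3% is not part of this point.

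**Conclusion.** The point holds as a mismatch between the planning rate and the endpoint, with a consequence that can be shown only as a range. The 80% applies to 3% anatomical apical recurrence, not to the composite failure tested at 1 and 5 years. With 55 evaluable women per arm, a 10-point margin and equal rates, power stays at 80% only up to about 3.6% failure (95% interval) or 3.0% (97.5% interval). Between 4.4% and 10% it runs from 72% down to 42%, or from 62% down to 31%. If non-inferiority must be shown at both time points, joint power cannot exceed the lower of the two.

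The results rest on the normal approximation, equal true rates, and an alpha the article does not state for the sample size. The 10% row is an assumption. The 4.4% row leans on a 10-week series, and the 6.9% row on an undefined cure rate. The article supports calling 3% optimistic for this endpoint, but not naming the rate that should replace it.

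**What to change.** In Sample size and power calculations, keep 3% as the historical basis of the 124, and say that it refers to anatomical apical recurrence and not to the composite primary endpoint. Add a short statement or table of the power that 55 evaluable women per arm give for the composite over a range of failure rates, for example 3% to 10%. Give it separately for 1 and 5 years, and at the confidence level actually used for the decision. Qualify the 80% accordingly, and reword the Abstract so that 62 per arm is described as the number needed under the 3% assumption.

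The cost is a few sentences and a less favourable stated power. Enrolment, endpoint, margin and decision rule are unchanged.
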